**Methods:**

This study is a protocol for a three-armed, single-blinded, placebo-controlled randomized controlled trial. Ninety participants scheduled for inguinal hernia repair will be randomly assigned to the TEAS group (*n* = 30), sham group (*n* = 30), and control group (*n* = 30). The TEAS group will receive treatment using four portable coin-sized electro-stimulators at both local and distal acupuncture points. The sham group will receive sham treatment with mock electrostimulation. The treatment groups will receive mixed frequency stimulation (alternating at 2 and 100 Hz every 3 s) in continuous mode for 30 min at intervals of 2 h for 24 h postoperatively. The control group will receive postoperative pain control using patient-controlled analgesia (PCA) device. The primary outcome is the total morphine dose received in the postoperative period (mg) using PCA 24 h after surgery. The number of PCA demands (i.e., times the button will be pressed) and delivered bolus doses, score on the Visual Analogue Scale, opioid-related side effects, the requirement for supplemental medications, score on the Hospital Anxiety and Depression Scale (HADS), and blood levels of stress hormones cortisol and prolactin.

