## Methods and analysis

### Study objective

The primary objective is to evaluate (a) the efficacy and (b) the safety of TEAS in reducing postoperative pain after inguinal hernia repair compared with sham and standard treatment. The secondary objectives include the assessment of pain intensity (Visual Analogue Scale), frequency of complications of opiates (e.g., sedation, pruritus, nausea, vomiting), anxiety and depression (Hospital Anxiety and Depression Scale), and levels of stress hormones (blood levels of cortisol and prolactin).

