### Randomization and blinding

Enrolled participants will be randomly assigned to TEAS, sham, or control group (1:1:1). An independent, blinded statistician will generate the block randomization scheme. The table will be managed by an independent researcher who is not involved in the recruitment, treatment, or assessment. The participants will be blinded to the type of treatment. Mock TEAS will be provided with the same lamplight as real TEAS, so the participants will not be able to predict the allocated group based on the appearance of the treatment (Fig. 1). The practitioners will be aware of the allocation arm while the subjects, outcome assessors, and statisticians performing the data analysis will be blinded to the treatment allocation. The schedule for the study is shown in Fig. 2.

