### Sample size justification

Power analysis was performed to determine the number of patients per group sufficient to.

detect a decrease of 30% or more in the PCA opioid analgesic requirements during the first 24 h after surgery, based on the results of the previous studies [13–15]. Each group will include 30 participants, a total of 90 participants. The proper size of the sample was calculated using the following formula:$$Sample\;size=\frac{Z_{1-a/2}{^2}p\left(1-p\right)}{d^2}$$

where:*Z*_1_ − _*a*/2_ is the standard normal variate (at 5% type 1 error *p* < 0.05), − 1.96;*p* is the expected prevalence obtained from a pilot study, − 0.26; and *d* is the absolute precision, − 0.05.

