### Statistical analysis

Quantitative variables will be reported using the mean and SD (M ± SD) for normally distributed data or median (Me), the lower quartile (Q1), and the upper quartile (Q3) and the range (Min–Max) for skewed data. Kolmogorov–Smirnov Normality Test will be used to verify the normality of distributions. Intergroup differences between the average values of the quantitative data will be assessed using the Student’s *t*-test (*t*-test for independents samples by groups) or Mann–Whitney *U* test. Kruskal–Wallis ANOVA will be used for multiple comparisons (post hoc tests). Additionally, a multivariate analysis, ANOVA for factorial designs (Factorial ANOVA), will be performed to analyze the main effects and their interactions (relationships between independent variables). Qualitative variables (nominal) will be represented as (*n*) and proportions (%). Independence of qualitative variables from the patient status will be verified by the chi-square test or Fisher’s exact test. The significance level will be set at 5%. All data will be analyzed using the Statistica v.13.3 (StatSoft).

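### The analysis section names an omnibus test as its post hoc procedure and does not say which of the two primary comparators decides efficacy

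*Protocol article*

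**What the plan says.** - **Objective (Protocol article, Study objective).** The primary objective is to evaluate TEAS "in reducing postoperative pain after inguinal hernia repair compared with sham and standard treatment". That is two comparators, with no order between them and no statement whether one or both must be beaten.
- **Endpoint (Abstract, Methods).** There is one primary endpoint: "The primary outcome is the total morphine dose received in the postoperative period (mg) using PCA 24 h after surgery".
- **Design (Randomization and blinding; Sample size justification).** "Enrolled participants will be randomly assigned to TEAS, sham, or control group (1:1:1"); "Each group will include 30 participants, a total of 90 participants".
- **Tests (Statistical analysis).** Differences between groups in quantitative data are assessed by Student's t-test or Mann–Whitney U. The next sentence says that Kruskal–Wallis "ANOVA will be used for multiple comparisons (post hoc tests"). A factorial ANOVA is then added for main effects and interactions.
- **Level (Statistical analysis).** "The significance level will be set at 5" per cent, without division between comparisons.

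**The concern.** Kruskal–Wallis asks whether the three groups differ at all. It does not say which pair differs, so it cannot be the post hoc step. As the only sentence on multiple comparisons names it in that role, the section states a multiplicity rule but states it wrongly. The two-sample tests are listed before it, and nothing makes them conditional on it. For the t-test route no one-way global test is named: the only parametric ANOVA is the factorial one, in a trial with a single three-level treatment factor.

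Two things are at stake. The first is the error rate across the two TEAS contrasts. The second is what a positive result would mean. The documents describe no device for control patients, so they will know that they receive no stimulation. Patients in the TEAS and sham groups are told that they receive current (Postoperative analgesia). The endpoint is morphine that patients request themselves. A difference from control could therefore reflect expectation alone. If that contrast could carry the trial, TEAS might be reported as effective without having beaten sham.

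**Working it through.** **Plan's own figures.** The plan gives no familywise error rate, only the 5% level, so there is none to reproduce. Its sample-size formula gives 1.96² × 0.26 × 0.74 / 0.05² = 295.6, so 296, not 30 or 90. That is a separate matter. It counts here only because the section gives neither an SD nor a power, so any power figure below is an assumption.

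**Inputs.**
- Two-sided 5%: the sample-size section uses the 1−α/2 quantile, 1.96, which "is the standard normal variate (at 5% type 1 error" describes. Sidedness is not stated for the tests themselves.
- 30 per arm, allocated 1:1:1. The two TEAS contrasts share the TEAS arm, so their test statistics have correlation 0.5 under the null.

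**Step 1. Ungated, unadjusted, either contrast suffices.** Let Φ₂ be the bivariate normal distribution function with correlation 0.5, and q = 1.96.
- P(neither significant) = Φ₂(q,q) − 2Φ₂(−q,q) + Φ₂(−q,−q) = 0.95462 − 2 × 0.02500 + 0.00462 = 0.9093.
- Two-sided familywise error = 1 − 0.9093 = 9.07%.
- False result favouring TEAS on at least one contrast = 1 − Φ₂(q,q) = 1 − 0.9546 = 4.5%, against 2.5% for one contrast.
- Simulation at 30 per arm with no effect agrees: 9.1% with t-tests (400,000 runs) and 9.05% with Mann–Whitney (100,000 runs). If the contrasts were independent the figure would be 1 − 0.95² = 9.75%.
- Counting all three pairs gives 12.2%, but that includes sham vs control.

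**Step 2. Other rules that the text could be meant to describe.**

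| Rule | Familywise error with no effect |
|---|---|
| Pairwise tests only after a significant Kruskal–Wallis test | 4.1% over the two TEAS pairs, 4.9% over all three |
| Both TEAS contrasts must be significant | 0.9%; at most 5% in any configuration |
| Each TEAS contrast at 0.025 (Bonferroni) | 4.65% |
| Each TEAS contrast at about 0.027 (Dunnett-type, critical z 2.212) | 5.0% |

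**Step 3. Power for the first contrast.** Two-sided t-test, 58 degrees of freedom, noncentrality (0.30/CV) × √(30/2), for the 30% reduction named in the sample-size section. The CV is assumed. At CV 0.4 the standardised difference is 0.75, and 0.75 × 3.873 = 2.905.

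| Assumed CV | α = 0.05 | α = 0.025 |
|---|---|---|
| 0.3 | 97% | 94% |
| 0.4 | 82% | 73% |
| 0.5 | 63% | 51% |
| 0.6 | 48% | 36% |
| 0.7 | 37% | 27% |

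Testing one contrast first at the full 5% keeps the middle column. Splitting α equally gives the right-hand one.

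**Step 4. Which contrast decides.** Suppose that TEAS equals sham and that both beat control by an assumed 0.3 to 0.5 SD through expectation alone. With 30 per arm, TEAS vs control is then significant in 21% to 48% of trials. This is not a type I error for that contrast, because the arms do differ. It shows why the rule for claiming efficacy has to name the contrast.

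**The case against.** The strongest reply is that the section never says the pairwise tests are unadjusted. Its sentence on multiple comparisons, however poorly worded, is a provision for multiplicity, and it may be shorthand for a Kruskal–Wallis test followed by rank-based pairwise comparisons. With three groups, a real gate holds the familywise error at about 5%. The word joining the two comparators in the objective can also be read as requiring both, which is conservative. A separate analysis plan, not shown, may set the adjustment and the order, and an article need not repeat them.

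Much of this stands. A reader might infer that the plan's chance of a false efficacy claim is 9% to 12%. The documents do not support that. The 9% needs three conditions together (no gate, no adjustment, either contrast sufficing), and none of them is written. The 12% counts sham vs control, which is not a claim for TEAS. Nor is it written that success may be declared on whichever contrast is positive.

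What does not fall away is that the one rule given is wrong as stated. The section does not leave multiplicity to another document; it assigns it to a test that cannot do the job. The gate reading also has to be supplied by the reader: there is no condition on significance, the pairwise tests come first, and the global test is labelled post hoc. Neither the gate nor a both-must-succeed rule would by itself make the sham contrast the deciding one in an either/or claim; only the both-must-succeed rule would require it to be won.

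**Conclusion.** The point holds in a limited form. The Statistical analysis section misnames a global test as its post hoc procedure and fixes no decision rule across the two comparators of the primary objective. The error rate for the primary endpoint is therefore undetermined: at or below 5% under a true omnibus gate or a both-must-succeed rule, and about 9% two-sided (4.5% against 2.5% in favour of TEAS) if the two contrasts are tested ungated and unadjusted and either suffices. These figures assume equal arms of 30 and no true effect. The power figures rest on an assumed CV and move widely with it. Severity is should-fix, with moderate confidence, because an analysis plan that is not shown may already settle the matter.

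**What to change.** For total PCA morphine over 24 h, state a fixed sequence:

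1. TEAS vs sham at two-sided 5%.
2. TEAS vs control at two-sided 5%, confirmatory only if step 1 is significant.

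Treat sham vs control as descriptive. Describe Kruskal–Wallis or ANOVA as a global test and delete the words in brackets that call it post hoc.

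This holds the familywise error at 5% and leaves the first contrast its full α, with no change to the sample size. A Dunnett-type threshold, an explicit gate or a both-must-succeed rule would also control the error. The sequence is preferred because it makes the sham contrast decisive at full α.

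The cost is a few sentences and one real drawback: if TEAS vs sham fails, TEAS vs control is exploratory only. Timing also matters. The Trial status section says recruitment was completed on 31/12/2020, so the rule counts as prespecified only if it is fixed before unblinded analysis. Otherwise it should be disclosed as a later decision. If an existing analysis plan already sets the order or adjustment, the article's wording should be brought into line with it.

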## Intervention

### Anesthesia protocol

A standard premedication of 7.5-mg oral midazolam will be administered in every patient, 30 min prior to entering the operating room. Thereafter, standard patient monitoring, including continuous electrocardiography, pulse oximetry, and indirect blood pressure (measured every 5 min), will be applied and maintained until the end of anesthesia. Three-minute preoxygenation with 100% oxygen will precede the induction phase in every patient. Then, 1–3mcg/kg fentanyl, followed by 2–3 mg/kg propofol and 0.6 mg/kg rocuronium, will be applied through the peripheral vein to induce general anesthesia. Individually selected, an appropriate size endotracheal tube (ET) would be placed via direct laryngoscopy. After confirmation of proper ET placement, mechanical ventilation will be commenced and anesthesia maintained by sevoflurane 2–4 vol% mixed with 60% oxygen, titrated to achieve 0.9–1.2 MAC. Continuous monitoring of capnography will ensure proper respiratory function and gas exchange. During the surgery, additional boluses of fentanyl (1–2mcg/kg) will be administered in the presence of the patient’s reactions to pain stimuli (i.e., tachycardia/hypertension). Depending on the time of surgery, an additional bolus of 25% of the initial dose of rocuronium might be applied. For basic pain control, 1 g of metamizole will be given to every patient before completion of the surgery. After cessation of sevoflurane administration and achieving an adequate level of consciousness and responsiveness, the patient will be extubated. After the surgery, every patient will be monitored and carefully observed for at least 30 min in the recovery room.

The surgical technique will be the Lichtenstein tension-free method. Hernia patients, according to the classification of Nyhus, were type II or IIIb.

### Postoperative analgesia

On a patient’s arrival in the postanesthesia care unit, the PCA device will be connected to the patient’s intravenous line and programmed to deliver 1-ml bolus doses of morphine (1 mg) “on-demand,” with a minimal lockout interval of 10 min and a maximum 4-h dose of 15 mg according to a standardized hospital protocol. PCA therapy will be initiated in the postanesthesia care unit when the patient was sufficiently alert to understand and operate the PCA device. If the patient requires pain medication prior to starting PCA therapy, an incremental dose of metamizole 1 g intravenously, will be administered by the postanesthesia care unit nursing staff. The postoperative PCA analgesic therapy will be supplemented with TEAS/sham therapy, which will start when the patient arrives in the postanesthesia care unit.

Stimulation will be performed using four portable coin-sized electro-stimulators (StimulAid Inc, Poland). A point-detection function in the device will confirm the correct localization of the stimulator. A combination of the LI4 acupuncture point and peri-incisional ashi points will be utilized to augment PCA analgesia in the postoperative period [16–18]. Not only point selection but also the frequency of stimulation and treatment timing play a critical role in determining the outcome of the intervention. Low-frequency (2 Hz) electrostimulation applied at the acupoints exerts antinociceptive effects mainly by enhancing the release of met-enkephalin (M-ENK), β-endorphin (β-EP), and dynorphin [19, 20]. Therefore, the TEAS group will receive mixed frequency stimulation (alternating at 2 and 100 Hz every 3 s) in continuous mode for 30 min at intervals of 2 h [19, 20]. The device will automatically shut off at the end of each 30-min treatment interval. The intensity of the stimulation will be adjusted to each individual to maintain a slight twitching of the regional muscle and achieve De-Qi sensations, such as soreness, distention, and heaviness. In both groups, electro-stimulators will be applied bilaterally to LI4 (He Gu) and ipsilateral to hernia to two ashi points located within a diameter of 5 cm from the incision site (Fig. 3). The sham group will be provided with the same devices as TEAS with the “in use” light flashing in the usual manner; however, the participants will be told that they may not be able to feel the electrical stimulation. The patients in TEAS and sham groups will be told that they are receiving current stimulation. The PCA therapy and TEAS/sham will be discontinued at 24 h.

**Fig. 3 Fig3:**
[figure not shown]
Acupuncture points of treatment. The stimulators will be placed bilaterally to LI4 (left) and ipsilaterally to hernia to two ashi points located within a diameter of 5 cm from the incision site

## Adverse events

All adverse events will be closely monitored through reports by participants or direct observation by personnel and by asking the patients about adverse events during the observation period. All adverse reactions will be recorded, and additional treatment will be offered if required. Serious adverse events will be reported to the ethics committee.

## Post-trial care

After the conclusion of a trial, the follow-up care will be provided by the patient’s personal physician.

## Data management

Demographic and clinical data will be gathered from all participants. All adverse events will be documented. Data will be collected by a surgical nurse and securely managed by the study coordinator. The data will be available only to investigators and to institutional or governmental auditors. The scientific research management committee will have access to the final trial dataset.

## Data monitoring and dissemination policy

Data and Safety Monitoring Board will evaluate the trial data periodically for integrity and to assure the safety of clinical trial participants. At the end of the study, the original data and results will be submitted to the scientific research management committee; they will be disclosed to the public after the results are published.

## Protocol amendments

If the protocol changes during the implementation of the study, researchers will communicate the important protocol modifications (e.g., changes to eligibility criteria, outcomes, analyses) to the relevant parties (e.g., investigators, REC/IRBs, trial participants, trial registries, journals, regulators).

## Discussion

The study aims to evaluate the efficacy and safety of TEAS for postoperative pain after inguinal hernia repair compared with sham and standard treatment. When planning a TEAS study, treatment timing, acupuncture points, and frequency of stimulation play a critical role in the outcome of the intervention. In several TENS and EA trials for postoperative pain, the number of stimulation sessions was limited to 4 or 5. It is likely that an intensified treatment protocol, which consists of multiple 30-min sessions at intervals of 2 h, will produce a more significant effect. To the best of our knowledge, this is the first study to examine an intensified stimulation protocol with TEAS in reducing analgesic consumption after surgery.

A mounting body of evidence suggests that acupuncture and acupuncture-related techniques can be performed before, during, or after surgery to alleviate postoperative pain [21]. TEAS or acupuncture-like TENS become more acceptable than acupuncture given its non-invasive character and similar analgesic effect [22, 23]. Also, the modality has several other advantages, such as programmable, fully automatic stimulation, ease of use, comfort and convenience for the patient, and minimal effort of medical personnel.

However, there is still scarce data to document the effects of TEAS on surgical pain [24, 25]. Adding the fact that it is easy to employ TEAS in a postoperative setting and that multiple stimulation sessions are possible, we planned to perform the trial to assess whether TEAS could be more effective in reducing the opioid requirement and improving patient comfort after surgery.

To maximize the effect of acupuncture treatment, we utilized both distal and local points. Several trials have used only distal points, including LI4 and ST36 [16–18], or only local points around the incision region [15]; however, a combination of points prove to exert a strong analgesic effect [14, 26]. Many clinicians assume that direct electrical stimulation around the incision region may lead to adverse events, but to date, there has not been any evidence of harmful effects such as increased pain or infection.

The limitation of our trial is that the assessors/medical personnel is not blinded. Due to the limits of the existing technology, we are unable to blind medical personnel. However, in the future, we may be able to utilize identical pre-programmed devices for sham and real group to resolve the blinding issue. Moreover, this trial is a single-center study. As the curative effect of TEAS may be affected by ethnicity and region, it will be essential to perform multicenter and large sample experiments in the future.

We anticipate that the results will determine whether TEAS with intensified stimulation protocol is a safe and effective option for reducing analgesic consumption and postoperative pain. The results of the study may serve as a platform for developing TEAS-based treatment regimens for enhanced recovery after surgery.

## Trial status

The study registration number is KB 599/2017 dated 21/07/2017. The first participant was enrolled on 01/01/2019. Recruitment was completed on 31/12/2020.

## Data Availability

The authors confirm that the data supporting the findings of this study are available within the article. The results will be disseminated in peer-reviewed journals and presented at international conferences.
